### Hypotheses and outcome measures

Primary hypotheses: The use of a relaxation tape by breastfeeding mothers starting at week 2 postpartum will result in:i.reduced maternal stress and anxietyii.the production of a higher volume of breast milkiii.lower milk cortisol concentrationsiv.favourable effects on infant behaviour (less crying, more sleeping)v.differences in infant body composition

Measures (i) - (v) will be assessed at baseline (week 2) and at 12 weeks in both control and intervention groups to ascertain the long-term effects of the relaxation therapy. Measures of (iii) will also be assessed pre and post a single breast-feed in both groups at 2, 6 and 12 weeks to ascertain the short-term effects of the relaxation therapy. The primary comparison will be the values at 12 weeks adjusted for the baseline value, compared between the two groups. Measures of body composition (v) will also be assessed at 14–16 weeks postnatally.

The primary outcomes will be assessed as follows:i)maternal stress and anxiety assessed using the Cohen’s Perceived Stress Scale (PSS) and Beck Anxiety Inventory (BAI) respectively (at 12 weeks)ii)breast milk volume at 12 weeks assessed non-invasively using stable isotope techniquesiii)breast milk cortisol concentrations at 12 weeksiv)infant behaviour measured using a 3-day diary at 6 weeksv)infant weight and body composition measured using stable isotopes at 12 weekschanges in maternal saliva cortisol, breast milk cortisol and milk volume before and after a breastfeeding session at 2, 6 and 12 weeks.

b) Secondary hypotheses:i.Infant temperament, behaviour and gender influence milk intake and hence early growth and body composition.ii.Milk composition including non-nutrient factors in breast milk (hormonal constituents; ghrelin and leptin) influence infant appetite and feeding patterns and hence infant growth and body composition

The secondary outcome measures will be:i.non-nutrient factors in breast milk – leptin and ghrelinii.macronutrient composition and milk energy (fat, carbohydrate, protein and total calorie)iii.infant temperament measured using the Revised-Infant Behaviour Questionnaire (R-IBQ)iv.infant appetite assessed using the Baby Eating Behaviour Questionnaire (BEBQ)v.maternal depression assessed using Edinburgh Postnatal Depression Scale (EPDS

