### Sample size and study population

The target sample population will be first-time mothers and their newborn infants living in Klang-Valley, Malaysia. The conventional formula [15] for two sample t-test is used to determine the number of infants required to detect a difference between two groups; control and intervention:$$ \mathrm{n}=16\ \left({\mathrm{SD}}^2/{\mathrm{D}}^2\right) $$where *n* = number per group, *SD* = standard deviation, *D* = difference between groups.

Hence, a sample of 56 infants (28 per randomised group) would allow the detection of a 0.76 SD difference in milk volume between groups at 80% power with a significance level of α = 0.05 (D = 0.76, SD = 1); this is a biologically plausible difference based on previous studies of the effect of relaxation interventions on milk volume production between control and intervention groups of mothers with preterm infants [13]. Since this study will involve mothers with healthy full-term infants, the effect size may be smaller than the previous study, as mothers with preterm infants are likely to be more stressed. Therefore, to allow for a smaller effect size as well as for drop-outs or failed measurements, it is planned that 80–100 pregnant women will be recruited.

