### Plan of statistical analysis

Data that are later found to be ambiguous will be flagged up and re-checked, and mothers will be contacted for clarification where necessary. Data will be recorded initially in Excel datasheets and later exported to SPSS. All questionnaires and anthropometric data will be analysed using IBM SPSS (version 23). Normality of continuous data will be assessed by Q-Q Plot, histogram and will also be tested by the Kolmogorov-Smirnov Test. The main analysis will be an intention-to-treat analysis comparing the difference between groups in the final outcome adjusted for the baseline value where data are available using independent t-tests. Independent t-test and repeated measures will be used to examine changes in milk intake and other milk components including cortisol levels between groups and between time points respectively as secondary analyses. For the secondary outcomes, associations between infant temperament/behaviour and milk volume, milk composition, infant growth and body composition will be examined using univariate analyses. Correlation and regression analysis/MANOVA will then be used to adjust for confounding factors. Interaction terms will be introduced where appropriate, especially in the multivariate analysis. The cut-off used for significance will be set at *p* < 0.05. Although multiple testing will be done to test the outcomes, the *p*-value cut-off point will not be adjusted for multiplicity since the different outcome measures are independent of each other.

Anthropometric data will be converted to standard deviation score (SDS, Z-score) for infant weight, height, head circumference and BMI using WHO 2006 standard data (LMS growth add- in for Microsoft Excel) and SDS will be used in all analyses. The weight data at the final time point will be compared between groups and adjusted for baseline weight as the primary outcome measure for growth using the LMS ‘Weight gain to SDS’ based on the WHO 2006 growth standard data (ie. external data). This method takes into account the baseline weight (HV1) in calculating the change from baseline to an endpoint or increase in weight between two-points of measurements. An increment of more than 1 band on the WHO growth chart or ±0.67 SD between measurements will be considered as representing ‘rapid weight gain’ [35].

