The composition of human milk varies across lactation, and between and within individuals diurnally and across a single feeding. Thus, milk sampling is an important issue, as there is a lack of consistency in sample collection in previous studies [37, 38]. One possible explanation for the inconsistent findings between published studies is the different methods used for sample collection (e.g. single spot sample or pooled milk sampling), as well as a lack of standardisation of timing with respect to both time of day or stage of lactation [37, 38]. This is especially important when measuring milk energy density in breast milk, as the changing fat content between fore- and hindmilk affects the total energy content. Presumably, this will also influence the content of other fat-soluble substances in breast milk, such as fat-soluble vitamins or other bioactive substances. To date, there is no universal sampling protocol or gold standard method for human milk sampling since there are various ethical aspects to be considered as well as limitations of the population and conditions in the field [38]. Thus, comparing data from different studies is challenging and problematic, especially for data that are based on a single milk sample collection. Hence, in this trial, fore- and hindmilk will be collected at 3 different time points and the milk sampling protocol will be standardised in terms of time and sampling method in order to minimise the variability. Moreover, unstandardized sample collection methods and different times for sampling may lead to unrepresentative samples being used during analysis. Therefore, in this trial, the isotope method will be used to estimate milk intake over a period of 14 days, which has the advantage of being physiological (ie. suckled breast milk), non-invasive (since it does not interfere with the breastfeeding process), and suited to free-living infants [32, 34].

In summary, the experimental design of this study aims to show causal relationships between maternal psychological state and infant behaviour and growth, which may be mediated through breast milk composition and/or volume. By investigating the mechanisms of biological and behavioural signalling during early human life, this project aims to provide a greater understanding of maternal-infant factors which influence BF outcomes. This may in turn allow identification of modifiable factors that can be useful targets for future interventions to increase breastfeeding duration.

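### The plan waives multiplicity adjustment across five primary outcomes because they are independent; that reason is unsound, the trial's own hypothesis contradicts it, and the family-wise error is left at about 18% to 23%

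*Protocol article*

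**What the plan says.** The section Plan of statistical analysis sets one threshold for all tests: "The cut-off used for significance will be set at *p* < 0.05". It concedes multiplicity ("Although multiple testing will be done to test the outcomes") and then states that the cut-off "will not be adjusted for multiplicity since the different outcome measures are independent of each other".

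The section Hypotheses and outcome measures numbers five primary outcomes:
- (i) maternal stress and anxiety, on two scales;
- (ii) milk volume at 12 weeks;
- (iii) milk cortisol at 12 weeks;
- (iv) infant behaviour from a 3-day diary, for which the hypothesis is "favourable effects on infant behaviour (less crying, more sleeping");
- (v) infant weight and body composition.

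An unnumbered item in the same list adds changes across a feed in saliva cortisol, milk cortisol and milk volume at three visits. The section names one primary comparison (12-week values adjusted for baseline, between groups), but no single primary outcome and no hierarchy.

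Only milk volume has a sample size: "a sample of 56 infants (28 per randomised group) would allow the detection of a 0.76 SD difference in milk volume between groups". The calculation takes a 5% significance level and 80% power.

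The Discussion says that the trial sets out to demonstrate "causal relationships between maternal psychological state and infant behaviour and growth, which may be mediated through breast milk composition and/or volume". The Background likewise calls the factors inter-related and hypothesises that maternal state is linked to milk production, which in turn affects infant feeding behaviour and growth.

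**The concern.** The stated reason fails in two ways. First, independence gives no protection. When each test carries a 5% error and the tests are independent, the errors accumulate almost additively; correlation is what would lessen the accumulation. Second, the premise contradicts the trial's own hypothesis. A design that looks for an effect running from maternal state through milk to the infant cannot also treat maternal stress, milk cortisol, milk volume, infant behaviour and infant growth as unrelated.

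At stake is how the results may be read. With five primary outcomes of equal standing and no rule for combining them, one p-value below 0.05 among several could be reported as a positive primary result, and the plan sets no bound on how often that would happen by chance.

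**Working it through.** **Inputs.** Per-test level 0.05 (Plan of statistical analysis). Five numbered primary outcomes (Hypotheses and outcome measures). D = 0.76, SD = 1, 28 per group (Sample size and study population). The article gives no correlations between outcomes, so those below are assumptions shown as a range. Two-sided testing is inferred from the factor 16 in the sample-size formula, since 2 × (1.96 + 0.84)² ≈ 15.7.

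**1. The plan's own figure.** n = 16 × 1² / 0.76² = 27.7, so 28 per group. Two-sample t-test power at 28 per group is 79.8%. The stated sample size is reproduced, for one outcome tested at 0.05.

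**2. Family-wise error under the plan's own premise.** For k independent tests it is 1 − 0.95^k.
- k = 5 (the numbered outcomes): 1 − 0.95⁵ = 22.6%.
- k = 7 (PSS and BAI counted separately, and weight counted apart from body composition): 1 − 0.95⁷ = 30.2%.

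**3. Family-wise error if the outcomes are correlated.** For k two-sided normal tests with common correlation r:

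| r (assumed) | 5 tests | 7 tests |
|---|---|---|
| 0 | 22.6% | 30.2% |
| 0.3 | about 21% | about 27% |
| 0.5 | about 18% | about 23% |

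Even at r = 0.9 the five-test figure is about 10%. Negative correlation also lowers it (21.7% at r = −0.2). Among jointly normal two-sided tests, independence is therefore the worst case (Šidák inequality). Under arbitrary dependence the bound is k × 0.05, or 25% for five tests.

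**4. What adjustment would cost in power for milk volume.** Two-sample t-test, 0.76 SD:

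| Level | 28 per group | 32 per group |
|---|---|---|
| 0.05 | 79.8% | 84.9% |
| 0.01 (equal Bonferroni, 0.05/5) | 57.2% | 64.9% |

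The second column of results is shown because the section Study design gives 64 dyads. Neither column allows for baseline adjustment, which could raise power.

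**The case against.** The best defence is that the trial is small and mechanistic, that its five hypotheses are distinct questions, and that each keeps its own 5% error. Part of that stands. Error per hypothesis is controlled, and nothing in the article says that one significant result makes the trial a success. A reader might infer that there is no type I error control at all. That goes too far: the family-wise rate is what is uncontrolled. But the article does not argue from distinct questions. It argues from independence, and its hypotheses are steps in one account of one intervention. A separate analysis plan may exist, but it would not make the printed reason sound.

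Two further strong readings are not supported.

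- A reader might count fifteen tests by splitting crying from sleeping and fat mass from fat-free mass, then adding two cortisol changes at three visits, and so reach 1 − 0.95¹⁵ = 53.7%. That count leaves out the within-feed change in milk volume, which the list names. It divides body composition into two tests that the list does not name. It also treats linked measures as independent: fat and fat-free mass add up to weight, and crying and sleeping share one 72-hour grid. The stated primary comparison, 12-week values adjusted for baseline, does not cover within-feed changes either.
- A reader might see a contradiction between the within-feed changes in the primary list and the analysis section, which treats changes in milk intake and milk components as secondary. That sentence speaks of differences between time points and mentions neither pre/post-feed changes nor saliva, so it may mean changes across visits. Their status is unclear; a contradiction is not established.

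**Conclusion.** The concern holds. The reason given for not adjusting is wrong as statistics and conflicts with the article's own Background and Discussion. For the five numbered primary outcomes the chance of at least one false positive is 22.6% under the plan's own assumption, and about 21% or 18% if the outcomes share a correlation of 0.3 or 0.5. With seven tests it is 30.2%, about 27% and about 23%. These figures assume two-sided, approximately normal tests and no true effect on any outcome in the family. The correlations are illustrative, but no value tried brings the rate near 5%.

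**What to change.** Delete the independence rationale and control the family-wise error.

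- **Preferred:** name 12-week milk volume as the single primary outcome, tested at 0.05. It keeps about 80% power for 0.76 SD at 28 per group. Report the other outcomes as secondary, either Holm-adjusted or as estimates with 95% confidence intervals and no confirmatory claim.
- **Acceptable alternatives:** a pre-specified fixed testing order that starts with milk volume, or Holm across the five primary outcomes. Either needs one named test per numbered outcome, or the extra tests counted in the family.
- **Not advised:** an equal Bonferroni split at 0.01, given the power loss shown above.

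Also state whether the unnumbered within-feed changes belong to the primary family.

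No extra participants or measurements are needed. The cost is still more than wording: the preferred route demotes four of the five primary hypotheses, and under any of these routes fewer outcomes can be called confirmatory. A fixed order carries the risk that nothing after a non-significant milk volume result can be claimed. Under Holm, power for milk volume would be at least the Bonferroni figure but could fall below 80%.

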## Discussion

The majority of the population in Malaysia, especially first-time mothers, practice a traditional postpartum confinement period for about 30–45 days, according to the cultural tradition of their ethnic background [36]. During this period, the mother and her infant will be taken care of either by their family members, particularly the infant’s grandmother, or by a confinement lady who will be paid to stay overnight with the mother or come to the house on a daily basis. The caretaker will usually prepare meals for breakfast, lunch and dinner following the cultural confinement diet for the mothers, and will also perform special postpartum traditional massage on the mother, especially during the first 3 weeks of the postnatal period [36]. The caretaker will also help to take care of the infant by changing the nappy, bathing or holding the infant when necessary. This is because the mother is encouraged to minimise physical activity and have ample rest to recover from the birth [36]. This confinement practice should facilitate the trial since all mothers in the study will receive similar care.

The composition of human milk varies across lactation, and between and within individuals diurnally and across a single feeding. Thus, milk sampling is an important issue, as there is a lack of consistency in sample collection in previous studies [37, 38]. One possible explanation for the inconsistent findings between published studies is the different methods used for sample collection (e.g. single spot sample or pooled milk sampling), as well as a lack of standardisation of timing with respect to both time of day or stage of lactation [37, 38]. This is especially important when measuring milk energy density in breast milk, as the changing fat content between fore- and hindmilk affects the total energy content. Presumably, this will also influence the content of other fat-soluble substances in breast milk, such as fat-soluble vitamins or other bioactive substances. To date, there is no universal sampling protocol or gold standard method for human milk sampling since there are various ethical aspects to be considered as well as limitations of the population and conditions in the field [38]. Thus, comparing data from different studies is challenging and problematic, especially for data that are based on a single milk sample collection. Hence, in this trial, fore- and hindmilk will be collected at 3 different time points and the milk sampling protocol will be standardised in terms of time and sampling method in order to minimise the variability. Moreover, unstandardized sample collection methods and different times for sampling may lead to unrepresentative samples being used during analysis. Therefore, in this trial, the isotope method will be used to estimate milk intake over a period of 14 days, which has the advantage of being physiological (ie. suckled breast milk), non-invasive (since it does not interfere with the breastfeeding process), and suited to free-living infants [32, 34].

In summary, the experimental design of this study aims to show causal relationships between maternal psychological state and infant behaviour and growth, which may be mediated through breast milk composition and/or volume. By investigating the mechanisms of biological and behavioural signalling during early human life, this project aims to provide a greater understanding of maternal-infant factors which influence BF outcomes. This may in turn allow identification of modifiable factors that can be useful targets for future interventions to increase breastfeeding duration.

## Abbreviations

BAI: Beck Anxiety Inventory
BEBQ: Baby Eating Behaviour Questionnaire
BF: Breastfeeding
EDD: Estimated delivery date
ELISA: enzyme-linked immunosorbent assay
EPDS: Edinburgh Postnatal Depression Scale
HV: Home visit
IFQ: Infant Feeding Questionnaire
IIFAS: Iowa Infant Feeding Attitude Scale
MANOVA: Multivariate analysis of variance
MOMS: Mother-Offspring Milk study
PSS: Perceived Stress Scale
RIBQ: Revised-Rothbart’s Infant Behaviour Questionnaire
